### 9.1.5 Early study termination by the sponsor

The study can be terminated by Vaxess at any time.

Reasons for early termination

- Unexpected, significant, or unacceptable safety risk to participants enrolled in the study
- Decision based on recommendations from applicable board(s) after review of safety and immunogenicity data
- Discontinuation of study drug development

In taking the decision to terminate, Vaxess will always consider participant welfare and safety. Should early termination be necessary, participants must be seen as soon as possible and treated as a prematurely withdrawn participant. The investigator may be informed of additional procedures to be followed in order to ensure that adequate consideration is given to the protection of the participant's interests. The investigator or sponsor depending on local regulation will be responsible for informing IRBs/IECs of the early termination of the trial.

## 9.2 Study completion and post-study treatment

Study completion is defined as when the last participant finishes their study completion visit and any repeat assessments associated with this visit have been documented and followed up appropriately by the investigator or, in the event of an early study termination decision, the date of that decision. Each participant will be required to complete the study in its entirety and thereafter no further study treatment will be made available to them.

The information collected is kept as source documentation. All SAEs reported during this time period must be reported as described in Section 10.1.3 SAE reporting. Documentation of attempts to contact the participant should be recorded in the source documentation.

## 10 SAFETY MONITORING AND REPORTING

### 10.1 Definition of adverse events and reporting requirements

#### 10.1.1 Adverse events

An AE) is any untoward medical occurrence (e.g. any unfavorable and unintended sign [including abnormal laboratory findings], symptom or disease) in a clinical investigation participant after providing written informed consent for participation in the study. Therefore, an AE may or may not be temporally or causally associated with the use of a medicinal (investigational) product.

The investigator has the responsibility for managing the safety of individual participant and identifying AEs.

Vaxess or designate qualified medical personnel will be readily available to advise on trial related medical questions or problems.

The occurrence of AEs must be sought by non-directive questioning of the participant at each visit during the study. AEs also may be detected when they are volunteered by the participant during or between visits or through physical examination findings, laboratory test findings, or other assessments.

Adverse events must be recorded under the signs, symptoms, or diagnosis associated with them, accompanied by the following information (as far as possible) (if the event is serious refer to Section 10.1.2 Serious adverse events):

1. The severity grade:
  - mild: usually transient in nature and not interfering with normal activities
  - moderate: sufficiently discomforting to interfere with normal activities
  - severe: prevents normal activities
2. Its relationship to the study treatment. If the event is due to lack of efficacy or progression of underlying illness (i.e. progression of the study indication) the assessment of causality will usually be 'Not suspected.' The rationale for this guidance is that the symptoms of a lack of efficacy or progression of underlying illness are not caused by the trial drug, they happen in spite of its administration and/or both lack of efficacy and progression of underlying disease can only be evaluated meaningfully by an analysis of cohorts, not on a single participant

3. Its duration (start and end dates) or if the event is ongoing, an outcome of not recovered/not resolved must be reported
4. Whether it constitutes a SAE (see Section 10.1.2 Serious adverse events for definition of SAE) and which seriousness criteria have been met
5. Action taken regarding with study treatment.

All adverse events must be treated appropriately. Treatment may include one or more of the following:

- Dose not changed
- Dose Reduced/increased
- Drug interrupted/withdrawn

6. Its outcome

Conditions that were already present at the time of informed consent should be recorded in medical history of the participant.

AEs (including lab abnormalities that constitute AEs) should be described using a diagnosis whenever possible, rather than individual underlying signs and symptoms.

Once an AE is detected, it must be followed until its resolution or until it is judged to be permanent (e.g. continuing at the end of the study), and assessment must be made at each visit (or more frequently, if necessary) of any changes in severity, the suspected relationship to the interventions required to treat it, and the outcome.

Information about known adverse reactions for the investigational drug can be found in the IB.

Abnormal laboratory values or test results constitute adverse events only if they fulfill at least one of the following criteria:

- they induce clinical signs or symptoms
- they are considered clinically significant
- they require therapy

Clinically significant abnormal laboratory values or test results must be identified through a review of values outside of normal ranges/clinically notable ranges, significant changes from baseline or the previous visit, or values which are considered to be non-typical in participant with the underlying condition or disease.

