|  | 
 
○ Standard descriptive demography. All participants who receive any investigational product will be included in the safety analyses.
 
○ Proportion of participants in each treatment group with any non-zero report will be tabulated for each local and systemic solicited and unsolicited reactogenicity event; groups will be compared by Fisher's exact test (alternatively, a Cochran-Mantel-Haenszel [CMH] test will be used to analyze events by ordinal severity category).
 
○ Participants with adverse events (including clinical laboratory abnormalities) will be summarized by Medical Dictionary for Regulatory Activities (MedDRA) body organ system and preferred term, severity, relatedness and, separately, by seriousness.
 
○ Proportion of participants in each treatment group with AE reports within each body organ system will be compared in the same manner. Significant heterogeneity will be probed at the preferred term level.
 
 
b) Immunogenicity Parameters
 
 
○ Sera collected will be analyzed for determination of HAI titers. Serum IgG anti-H1 HA, virus microneutralization titers, serum IgE and anti-silk fibroin by Enzyme-linked immunosorbent assay (ELISA) will be assessed on (vaccination day), and on Days 29 (<math>\pm 1</math>), and 180 (<math>\pm 5</math>).
 
 
The results of these determinations will be evaluated as follows:
 
 
● Calculation of the geometric mean of pre- and post-vaccination HAI and anti-H1 HAI IgG serum antibody titers for each treatment group.
 
● Change from pre- to post-vaccination in geometric mean HAI and anti-H1 HAI IgG titers for each treatment group.
 
● Seroconversion rate defined as percentage of participants with either a pre-vaccination HAI titer <math>< 1:10</math> and post vaccination HAI titer of <math>\geq 1:40</math> or a pre-vaccination HAI titer of <math>\geq 1:10</math> and a minimum four-fold rise in post vaccination HAI antibody titer at each timepoint.
 
● Seroprotection rate defined as the percentage of participants with a HAI titer <math>\geq 1:40</math> at each timepoint
 
● Calculation of the geometric mean of pre- and post-vaccination influenza virus microneutralization titers
 
● Change from pre- to post-vaccination in geometric mean microneutralization titers
 
● Calculation of the geometric mean of pre- and post-vaccination anti-silk fibroin serum IgG antibody titers for each treatment group.
 
● Change from pre- to post-vaccination in geometric mean anti-silk fibroin IgG titers
 
● Calculation of the geometric mean of pre- and post-vaccination total serum IgE titers
 
● Change from pre-to post-vaccination in geometric mean total IgE titers
 
 |

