## 10.2 Additional Safety Monitoring

| SERUM                                                | Mild: Grade 1 | Moderate: Grade 2 | Severe: Grade 3 | Potentially Life Threatening: Grade 4 |
|------------------------------------------------------|---------------|-------------------|-----------------|---------------------------------------|
| ALT, AST (liver function tests) increase by a factor | 1.1-2.5 x ULN | 2.6-5.0 x ULN     | 5.1-10 x ULN    | >10 x ULN                             |
| Cr mg/dL                                             | 1.5-1.7       | 1.8-2.0           | 2.1-2.5         | >2.5                                  |
| Blood Urea Nitrogen- BUN mg/dL                       | 23-26         | 27-31             | >31             | Dialysis                              |

- The laboratory values serve as a guide and are dependent on the institutional reference ranges.

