#### **Adverse events**

All information obtained on AEs will be displayed by treatment group, ethnicity, and participant.

The number (and percentage) of participants with treatment-emergent AEs (events started on or after the dose of study medication or events present prior to start of treatment but increased in severity on or after the dose of study medication based on preferred term) will be summarized in the following ways:

- by treatment, ethnicity, primary system organ class and preferred term.
- by treatment, ethnicity, primary system organ class, preferred term and maximum severity

Separate summaries will be provided for study medication related AEs, death, SAEs, other significant AEs leading to discontinuation.

A participant with multiple AEs within a primary system organ class is only counted once towards the total of the primary system organ class.

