\* The laboratory values provided in the tables serve as guidelines and are dependent upon institutional normal parameters. Institutional normal reference ranges should be provided to demonstrate that they are appropriate.

\*\* The clinical signs or symptoms associated with laboratory abnormalities might result in characterization of the laboratory abnormalities as Potentially Life Threatening (Grade 4). For example, a low sodium value that falls within a grade 3 parameter (125-129 mEq/L) should be recorded as a grade 4 hyponatremia event if the subject had a new seizure associated with the low sodium value.

\*\*\* ULN” is the upper limit of the normal range.

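### For unsolicited laboratory and vital-sign adverse events, Section 10.1.1 grades severity by effect on activities, Section 10.2 and Appendix 3 by measured value, and nothing says which grade is recorded

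*Protocol*

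**What the plan says.** Section 10.1.1 defines an adverse event so as to cover "any unfavorable and unintended sign [including abnormal laboratory findings], symptom or disease". Each event is to be recorded with a severity on three levels. The lowest is "mild: usually transient in nature and not interfering with normal activities", the highest is "severe: prevents normal activities", and the middle level also turns on interference with activities. There are no numeric grades, no fourth level and no exception for findings made by measurement.

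The same section limits when an abnormal laboratory value becomes an adverse event. It must meet at least one of three criteria: it causes signs or symptoms, it needs therapy, or, in the protocol's words, "they are considered clinically significant". Symptoms are therefore not required.

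Section 10.2 gives a four-grade table whose first row is "ALT, AST (liver function tests) increase by a factor", followed by creatinine and BUN. It is described as a guide. Appendix 3 has four-grade tables for vital signs, hematology, serum chemistry and urine. A footnote to the serum table says that "a low sodium value that falls within a grade 3 parameter (125-129 mEq/L) should be recorded as a grade 4 hyponatremia event" if the participant had an associated new seizure.

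On the analysis side, Section 12.4.1 makes all safety data primary endpoints. The synopsis lists among the safety parameters "Participants with adverse events (including clinical laboratory abnormalities) will be summarized by Medical Dictionary for Regulatory Activities (MedDRA", and goes on to name severity as one of the summary dimensions. Section 12.4.2 tabulates treatment-emergent events "by treatment, ethnicity, primary system organ class, preferred term and maximum severity". Neither place names the severity scale.

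**The concern.** Two scales apply to one finding and answer different questions. A laboratory abnormality is usually found by measurement and often has no effect on what the participant does that day. A scale built only on activities puts it at the bottom, however extreme the value. The Appendix 3 footnote shows that the value-based grade is meant to be recorded for an event, and it uses a level that Section 10.1.1 does not have.

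At stake is the table of adverse events by maximum severity, which belongs to the primary endpoint of a first-in-human study. If investigators follow Section 10.1.1, the table understates severity for the findings that scheduled laboratory draws exist to detect. If some follow Section 10.1.1 and others Appendix 3, like events are graded differently across up to three sites. The recorded grade is the investigator's entry, so an analysis plan cannot make it consistent afterwards. Laboratory grades could be derived separately from the values, but that would be another variable beside the recorded severity.

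**Working it through.** The plan states no figure on this point, so the check sets the scales side by side.

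Inputs: the three levels in Section 10.1.1; the Grade 1 to 4 bands in Section 10.2 and Appendix 3; 15 participants per arm (Table 2).

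Step 1, whether the event enters the table. Take a finding without symptoms that the investigator judges clinically significant. It is an adverse event under Section 10.1.1.

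Step 2, its grade on each scale, assuming no effect on activities. Under Section 10.1.1 only the lowest level fits, because the other two require interference.

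| Finding | Section 10.1.1 | Value-based grade | Source | Gap |
|---|---|---|---|---|
| ALT 8 x ULN | mild (1) | 3 (band 5.1-10 x ULN) | 10.2 and Appendix 3 | 3 - 1 = 2 |
| ALT above 10 x ULN | mild (1) | 4 | 10.2 and Appendix 3 | 4 - 1 = 3 |
| Creatinine 2.1-2.5 mg/dL | mild (1) | 3 | 10.2 and Appendix 3 | 3 - 1 = 2 |
| Platelets 25,000-99,000 per mm3 | mild (1) | 3 | Appendix 3 | 3 - 1 = 2 |
| Systolic pressure above 155 mmHg, recorded as an event | mild (1) | 3 | Appendix 3 | 3 - 1 = 2 |

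Step 3, where the conflict stops.
- Section 10.2 has no vital signs; their scale is in Appendix 3 only.
- Grade 4 for a vital sign mostly requires an emergency visit, hospitalization or intubation. Fever above 40 °C is the exception. The asymptomatic Grade 4 case is therefore mainly a laboratory one.
- Some laboratory Grade 4 entries, such as dialysis for BUN, are also not defined by value.
- Solicited reactions are scored with Appendices 1 to 3 (Table 5 and Table 6), so the exposed group is unsolicited events.

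Step 4, weight in a table. One participant moved between categories is 1/15 = 6.7% of an arm. This is the resolution of the table, not an estimate of how often the misgrading would occur.

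Step 5, the stopping rules in Section 9.1.4. Two entries use a numeric grade for adverse events: withdrawal after a grade 3 event, and a grade 3 unsolicited event. Each triggers at one participant, and Section 10.1.1 defines no numeric grade. The laboratory limb of the second row refers to a grade 3 abnormality in the parameter itself and so does not depend on the adverse-event severity scale.

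**The case against.** The best case for the plan is that the specific scale governs over the generic one. Table 6 assigns systemic safety measures to Appendix 3. Footnote m of Table 5 sends to standard collection only events that the solicited appendices do not cover. The Appendix 3 footnote is itself an instruction on recording. On that reading Section 10.1.1 applies only where no scale exists. The exposure is also narrow: the laboratory value must be judged significant or treated, and standard collection ends at Day 29. Laboratory data are also listed, flagged and shown in shift tables, so the abnormality is not lost. The choice of severity variable for a table is commonly left to an analysis plan.

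Much of this stands. It removes solicited events from the point and limits its size. It does not settle it. Footnote m divides collection and says nothing about severity. Section 10.1.1 expressly includes laboratory findings and carves nothing out. The Day 29 laboratory draw falls inside the collection period but outside solicited scoring. The shift tables use low, normal and high, not grades. The conflict is in the recording rule, which the protocol itself fixes.

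A reader might infer that an ALT of 8 x ULN recorded as mild would escape the stopping rules. The documents do not support this, because the laboratory limb in Section 9.1.4 and the synopsis grades the value. A reader might also infer that every adverse event is affected, or that asymptomatic Grade 4 vital signs are generally recorded as mild. Neither follows, for the reasons given at step 3 of the check.

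**Conclusion.** The inconsistency is real and should be corrected, but it is confined. It concerns unsolicited laboratory events that are asymptomatic yet clinically significant or treated (Grade 3 or 4), and unsolicited vital-sign events (mainly Grade 3). For these, Section 10.1.1 taken literally records a severity two categories below the value-based grade, or three for laboratory values at Grade 4. The effect falls on the adverse-event table by maximum severity and on consistency between sites.

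This rests on two assumptions: that such findings usually do not disturb activities, and that at least some investigators apply Section 10.1.1 as written. The documents give no frequency, so the expected number of misgraded events cannot be stated. Separately, the two stopping entries for grade 3 adverse events use a term that Section 10.1.1 does not define.

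**What to change.** In Section 10.1.1, state three things:
- Where Section 10.2 or Appendices 1 to 3 give a scale for the finding, that grade, including Grade 4, is the severity recorded on the adverse-event page.
- The functional definition applies only to events without such a scale.
- How mild, moderate and severe correspond to Grades 1 to 3, so that all events share one recorded variable.

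In Section 12.4.2, name that recorded grade as the severity used in the tables.

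The stopping entries for a grade 3 adverse event and a grade 3 unsolicited adverse event, in Section 9.1.4 and the synopsis, must be reconciled with Section 10.1.1 by the sponsor. This review does not propose what they should mean. The laboratory limb needs no change for this purpose.

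The cost is a few sentences, a completion guideline for the adverse-event page and a severity field that accepts Grade 4. The count of severe events may rise slightly.

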### 10.1.2 Serious adverse events

A SAE is defined as any adverse event [appearance of (or worsening of any preexisting)] undesirable sign(s), symptom(s), or medical condition(s) which meets any one of the following criteria:

- fatal
- life-threatening

Life-threatening in the context of a SAE refers to a reaction in which the participant was at risk of death at the time of the reaction; it does not refer to a reaction that might have caused death if it were more severe (please refer to the ICH-GCP Guidelines).

- results in persistent or significant disability/incapacity
- constitutes a congenital anomaly/birth defect
- requires inpatient hospitalization or prolongation of existing hospitalization, unless hospitalization is for:
  - social reasons and respite care in the absence of any deterioration in the participant's general condition
  - treatment on an emergency outpatient basis for an event not fulfilling any of the definitions of a SAE given above and not resulting in hospital admission
  - is medically significant, e.g. defined as an event that jeopardizes the participant or may require medical or surgical intervention to prevent one of the outcomes listed above

Medical and scientific judgment should be exercised in deciding whether other situations should be considered serious reactions, such as important medical events that might not be immediately life threatening or result in death or hospitalization but might jeopardize the participant or might require intervention to prevent one of the other outcomes listed above. Such events should be considered as “medically significant.” Examples of such events are intensive treatment in an emergency room or at home for allergic bronchospasm, blood dyscrasias, or convulsions that do not result in hospitalization or development of dependency or abuse (please refer to the ICH/GCP Guidelines).

All new malignant neoplasms will be assessed as serious under “medically significant” if other seriousness criteria are not met.

Any suspected transmission via a medicinal product of an infectious agent is also considered a serious adverse reaction.

All reports of intentional misuse and abuse of the product are also considered serious adverse event irrespective if a clinical event has occurred.

### **10.1.3 SAE reporting**

To ensure participant safety, every SAE, regardless of causality, occurring after the participant has provided informed consent and until the study completion visit or 30 days after end of trial for participants who stopped study early must be reported to Vaxess safety within 24 hours of learning of its occurrence. Detailed instructions regarding the submission process and requirements are to be found in the investigator folder provided to each site.

All follow-up information for the SAE including information on complications, progression of the initial SAE and recurrent episodes must be reported as follow-up to the original episode within 24 hours of the investigator receiving the follow-up information. An SAE occurring at a different time interval or otherwise considered completely unrelated to a previously reported one must be reported separately as a new event.

If the SAE is not previously documented in the IB (new occurrence) and is thought to be related to the study treatment, a safety associate may urgently require further information from the investigator for health authority reporting. Vaxess may need to issue an Investigator Notification (IN) to inform all investigators involved in any study with the same study treatment that this SAE has been reported.

Suspected Unexpected Serious Adverse Reactions (SUSARs) will be collected and reported to the competent authorities and relevant ethics committees in accordance with EU Guidance 2011/C 172/01 or as per national regulatory requirements in participating countries.

#### **Screen failure participants**

SAEs occurring after the participant has provided informed consent until the time the participant is deemed a Screen Failure must be reported to Vaxess or designate.

#### **Randomized or treated participants**

SAEs collected between time participant signs ICF until end of study (participant has completed study or stopped study early).

Any SAEs experienced after the end of study should only be reported to Vaxess or designate Safety if the investigator suspects a causal relationship to study treatment.

